### Sample size {14}

The sample size/power calculation is based on a retrospective single-center study and literature review [14].

In this single-center study, 38 patients received pDC and 49 received the best medical treatment, whereas 14 of them underwent secondary DC due to intractably elevated ICP. After 2 years, 10 out of 38 (26%) patients who underwent pDC achieved a favourable outcome compared with 10 out of 49 (20%) patients in the control group (*p*=0.61). In a systematic review of the literature and after selection, 64 out of 131 patients who underwent pDC (49%) achieved a favourable functional long-term outcome.

Simulation analyses showed that the planned Mantel-Hanzel test will have a power of 80% to detect an improvement of the rate of patients with the favorable outcome from 30% under the control intervention to 50% under pDC if the sample size is 102 patients per group. The simulations were performed, assuming minimum six centers. To account for the loss of information due to possible dropouts, 216 patients will be included in the study.

### Recruitment {15}

As SAH is an emergency, no designed recruitment strategy could be implemented. Thus, every patient suffering an aneurysmal SAH and being admitted to one of the participating hospitals (see above) will be screened for eligibility.

## Assignment of interventions: allocation

### Sequence generation {16a}

The allocation to the treatment group will be performed electronically. The subject will be enrolled into the study using the randomization tool of the electronic case report form (eCRF) system called RedCap. The randomization is performed blockwise in a 1:1 ratio to experimental intervention versus control intervention. The randomization will be stratified by trial site.

### Concealment mechanism {16b}

The allocation to the treatment group is concealed by the usage of an electronic randomization tool in the eCRF system.

### Implementation {16c}

The allocation sequence is generated randomly by the computer-based “RedCap” randomization tool implemented by the statistician of the Clinical Study Core Unit Bonn (SZB). After input of all data necessary for randomization (inclusion/exclusion criteria, demographic data), the electronic system displays the randomization result.

## Assignment of interventions: blinding

### Who will be blinded {17a}

Randomization will be open, and only raters for assessment of mRS will be blinded.

### Procedure for unblinding if needed {17b}

Not applicable.

## Data collection and management

### Plans for assessment and collection of outcomes {18a}

Assessment of the initial mRS as well as the baseline characteristics, outcome, and other trial data will be performed by the local investigator supported by a study nurse (e.g., laboratory parameters etc.) and will be documented in the eCRF.

### Plans to promote participant retention and complete follow-up {18b}

Contact data (e.g., address, phone numbers) for each participant and their next of kin (if allowed) will be obtained after recruitment to ensure complete follow-up. We will reschedule phone calls if the participant requests this. Most of the other data (e.g., vital parameters, length of ICU stay, etc.) will be provided by the hospital information system collected in accordance with the indispensable (ICU) treatment.

### Data management {19}

Data management of the study will be carried out by the SZB (section IMBIE (see below)). The study data is recorded and stored in a suitable, validated Clinical Data Management System (CDMS). Details on data management (procedures, responsibilities, data corrections, if any, which may be made by Data Management staff themselves, etc.) will be described in a data management plan prior to the trial. During the trial, the performance of data management and any deviations from the data management plan will be documented in a data management report. Before any data entry is performed, the trial database will be validated and the technical specifications of the database will be documented in a variable plan.

### Confidentiality {27}

The collection, transmission, archiving, and evaluation of personal data in this clinical trial are performed according to local applicable laws (Data Protection Act, General Data Protection Regulation). Prior to trial participation, each subject must be informed by the investigator about the purpose and extent of the collection and use of personal data, particularly medical data, and must give written informed consent.

The subjects must be informed that any subject-related data in this trial are handled confidentially and will be captured in pseudonymized form (subject ID number for the trial, year of birth) and will only be transmitted to the project leaders/data monitoring safety board for scientific and adverse event evaluation as well as the responsible ECs of the trial sites for verifying the proper conduct of the trial and for assessment of trial results and adverse events. During monitoring, audits, or inspections, representatives of the sponsor (monitor, auditor) or of the local regulatory authority(ies) must have direct access to personal data. In this case, the investigator is released from confidential medical communication.

### Plans for collection, laboratory evaluation, and storage of biological specimens for genetic or molecular analysis in this trial/future use {33}

Not applicable as no biological specimens will be collected or used for genetic or molecular analysis in this trial.

## Statistical methods

### Statistical methods for primary and secondary outcomes {20a}

Statistical analysis will be performed at the Institute of Medical Biometry, Informatics and Epidemiology (IMBIE) at the University of Bonn Medical Center. The rate of a favorable outcome will be compared between the treatment groups with a two-sided Mantel-Hanzel test at a level of 5%, stratifying for centers. The overall effect of therapy will be assessed by the calculation of a Mantel-Hanzel overall odds ratio with 95% confidence limits. For this analysis, the outcome of all patients with missing data for the primary outcome at 12 months will be counted as unfavorable.

This analysis will be repeated based on the PP population. Relevant differences between the results of ITT and PP analysis have to be critically discussed.

Mortality will be analyzed by calculating Kaplan-Meier estimators for survival in both treatment groups. Mortality after 7 and 90 days and after 12 months will be derived from the Kaplan-Meier estimators with 95% confidence limits.

Additional details of the statistical analysis will be specified in the statistical analysis plan of the trial.

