## Introduction

### Background and rationale {6a}

Poor-grade aneurysmal subarachnoid hemorrhage (SAH), defined as grades 4 and 5 according to the World Federation of Neurosurgical Societies (WFNS) [1], is associated with poor neurological outcome and high mortality [2–5].

The rupture of an intracranial aneurysm can cause brain swelling primarily due to severe damage of brain tissue and secondarily due to vasospasm followed by infarction that both leads to elevation of intracranial pressure (ICP). Studies have shown that brain swelling and elevated ICP are known to worsen outcomes following SAH [6–8]. Despite this, significant predictors of unfavorable outcomes in patients with poor-grade SAH are patient age, WFNS grade 5, signs of cerebral herniation, aneurysm size, and space-occupying hematoma [9].

Decompressive craniectomy (DC) is a well-established surgical intervention aiming to reduce increased ICP. After traumatic brain injury (TBI) and space-occupying stroke, DC has been shown to successfully reduce elevated ICP and also improve patient’s outcome in those strokes [10–13].

Besides a proven lifesaving effect in general, it is still debatable if an early decompression within 24 h after SAH—i.e., primary DC (pDC)—provides a better long-term functional outcome with lower rates of severe disability and dependency rates of patients or leads to a higher number of survival with dependent patients. A retrospective series of patients treated with a pDC in poor-grade SAH indicates that a pDC may be warranted in this severely ill subset of patients [14]. However, despite these promising data, there are no data from randomized controlled trials proving or disproving the beneficial effect of pDC, a rather aggressive surgical treatment compared to a neuro-intensive medical therapy with a secondary DC only performed if ICP cannot be handled by other treatment options [15–34].

Thus, we aim to investigate the effect of pDC in a prospective randomized trial regarding the mortality rate and the degree of disability of these patients.

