## Methods: participants, interventions, and outcomes

### Study setting {9}

The trial will be conducted in 9 centers in Germany which must meet the structural and personnel requirements for performing the planned regular trial-related investigations (Fig. 2).

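### The primary analysis adjusts for centre only; adding age and WFNS grade, both known before allocation, would gain a modest amount of power and protect against chance imbalance

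*Protocol article*

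**What the plan says.** In the protocol article, the section on statistical methods for primary and secondary outcomes {20a} has the rate of favourable outcome (mRS 0–4 at 12 months) "compared between the treatment groups with a two-sided Mantel-Hanzel test at a level of 5%, stratifying for centers". The effect measure is the "calculation of a Mantel-Hanzel overall odds ratio with 95% confidence limits". No covariate appears in either. The section on additional analyses {20b} plans none.

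On allocation, section {16a} says: "The randomization will be stratified by trial site". No other stratification factor is named.

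On prognosis, section {6a} says that "significant predictors of unfavorable outcomes in patients with poor-grade SAH are patient age, WFNS grade 5, signs of cerebral herniation", followed by aneurysm size and space-occupying hematoma. Age limits and WFNS grade 4 or 5 are inclusion criteria {10}. Under {16c}, eligibility and demographic data are entered before the allocation is shown.

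On sample size, section {14} states that "the planned Mantel-Hanzel test will have a power of 80" per cent to detect an improvement "from 30% under the control intervention to 50% under pDC if the sample size is 102 patients per group", raised to 216 in total for dropout. It adds: "The simulations were performed, assuming minimum six centers". Section {9} states: "The trial will be conducted in 9 centers in Germany".

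**The concern.** The protocol names strong predictors of its outcome, determines two of them before randomisation, and then uses neither in the design or the primary analysis. Two things follow.

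- **Power.** For a binary outcome, adjusting for prognostic baseline variables raises the power of the treatment test at the same number of patients. A centre-only test forgoes that gain.
- **Chance imbalance.** Nothing in the allocation balances WFNS grade within site, and nothing in the analysis corrects an unlucky split. If pDC happened to receive more grade 5 patients, its observed benefit would shrink; with fewer, it would be flattered. An adjusted analysis chosen after the imbalance was seen would be post hoc.

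**Working it through.** **1. Reproduce the plan's figure.** Inputs from {14} and {20a}: 30% vs 50%, two-sided 5%, power 80%, 1:1.

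Without continuity correction: n = [1.960·√(2·0.40·0.60) + 0.842·√(0.30·0.70 + 0.50·0.50)]² / 0.20² = (1.358 + 0.571)² / 0.04 = 93 per group.

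With continuity correction: (93/4)·[1 + √(1 + 4/(93·0.20))]² = 102.8, so 103 per group.

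The stated 102 matches the corrected version. Simulating the centre-stratified Mantel-Haenszel test at 204 patients (blocks of 4, 6,000 runs, homogeneous centres) gives:

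| Centres | With correction | Without correction |
|---|---|---|
| 6 | 0.800 | 0.840 |
| 9 | 0.794 | 0.835 |

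The sample size stands. At 216 patients and 9 centres, the uncorrected test simulates at about 85%.

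**2. Gain from adding age and WFNS grade.** The article gives no predictor strengths and no share of grade 5. The assumptions are 50% grade 5, an odds ratio for unfavourable outcome of 1.5 to 4 for grade 5, and 1.3 to 2 per SD of age. Marginal rates are held at 30% and 50%, with 204 patients and 3,000 to 4,000 runs. To isolate the covariates, both columns use a likelihood-ratio test from logistic regression.

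| OR grade 5 / OR per SD age | Centre only | Centre + WFNS + age | Gain (points) |
|---|---|---|---|
| 1.5 / 1.3 | 0.845 | 0.852 | about 1 |
| 2 / 1.5 | 0.836–0.844 | 0.862–0.865 | 2 to 3 |
| 3 / 1.5 | 0.850–0.854 | 0.876–0.887 | 2 to 4 |
| 4 / 2 | 0.840–0.844 | 0.900–0.909 | about 6 |

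The simulation standard error of one such power is about √(0.85·0.15/3,000) = 0.0065, so the weakest-case gain is about the size of the noise. A separate simulation at 216 patients and 9 centres put the like-for-like gain at about 0.5 to 5 points.

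**3. Type I error under the null.** The uncorrected centre-only Mantel-Haenszel test gave 0.041–0.054, and the corrected one 0.027–0.037. The adjusted likelihood-ratio test gave 0.049–0.062, so it can run slightly high.

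**4. Chance imbalance in WFNS grade.** With half the patients grade 5, the SD of the between-arm difference is √(2·0.25/108) = 6.8 points at 108 per arm. In simulations at 204 patients, the arms differed by 10 points or more, in either direction, in about 13% to 15% of trials. When the excess fell on pDC, the mean observed benefit was about 16 to 18 points instead of 20. In those trials:

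| OR grade 5 / OR per SD age | Mantel-Haenszel, centre only (uncorrected) | Adjusted |
|---|---|---|
| 2 / 1.5 | 0.73–0.74 | 0.85–0.87 |
| 3 / 1.5 | 0.73–0.74 | 0.91–0.92 |
| 4 / 2 | 0.64–0.65 | 0.88–0.90 |

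These are small subsets of the runs, so the figures are approximate.

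**5. Staying with Mantel-Haenszel.** Adding WFNS as a further stratum to centre gains only about 0 to 2 points.

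**The case against.** The strongest reply is that nothing here is wrong. The analysis stratifies by the factor used in randomisation and is the test that the sample size was built on. It holds its type I error and reaches its target. That is correct, and it rules out three stronger readings that a reader might infer.

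- **That the trial is underpowered or the test invalid.** Steps 1 and 3 show neither. Over all randomisations, the error rate of the planned test already allows for chance imbalance. The adverse splits in step 4 are a minority of trials and rest on an assumed 50% grade 5.
- **That adjustment buys 7 to 11 points.** That gap appears against the continuity-corrected test, and about 4 points of it come only from dropping the correction. Against the uncorrected test, about 1 point comes only from moving to a likelihood-ratio logistic test.
- **That the data are certainly in hand.** Age is. For WFNS, grade 4 or 5 is a single eligibility criterion and the visit schedule has no row for it. Storing the grade separately is likely but not stated.

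Two practical objections also stand. The adjusted model has 12 coefficients (intercept, 8 centre terms, arm, age, WFNS) for about 0.40·216 = 86 favourable outcomes. With centres assumed to range from 4 to 60 patients, at least one centre had identical outcomes throughout in about 26% of simulated trials under 30% vs 50%, and in about 45% under the null. Mantel-Haenszel copes with such centres; fixed centre effects need a stated rule. Also, treatment is open {17a} and recruitment began in October 2019, so a change made merely before formal unblinding gives weak protection.

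The analysis plan, which is not shown, could add an adjusted sensitivity analysis. It cannot be said that no such analysis exists anywhere. But the article already fixes the primary test, its stratification factor and its effect measure, so this point concerns a stated choice and not deferred detail.

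**Conclusion.** The point holds as one of efficiency and robustness. Centre is the only factor in both allocation and primary analysis, although the protocol names age and WFNS grade 5 as significant predictors and determines both before allocation. The cost is about 0.5 to 6 points of power like for like at 204 to 216 patients, plus an uncorrected chance imbalance in grade with an SD of about 6.8 points between arms. Both figures rest on assumed inputs: half the patients grade 5, and the predictor strengths in step 2. The source of the predictor claim may also have defined unfavourable outcome differently from mRS 5–6, so the true gain could lie at the low end. The change is worth making because it needs no extra patients or visits, not because the planned analysis fails.

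**What to change.** Before any outcome data by arm are reviewed, amend the primary analysis as follows.

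- Use logistic regression of favourable outcome on arm, centre, age (continuous) and WFNS grade (4 vs 5), tested at two-sided 5%.
- State the rule for small centres: pooling, a random centre effect or a penalised fit. Name the exact test and check its type I error by simulation at realistic centre sizes, given step 3.
- Record grade 4 vs 5 as a separate field if it is not already stored that way.
- Report a standardised risk difference with 95% CI beside the adjusted odds ratio. The latter is conditional on the covariates and differs in scale from the Mantel-Haenszel odds ratio.
- Keep the centre-stratified Mantel-Haenszel test as a supporting analysis. Do not replace it with strata of centre by WFNS, which are sparse and recover little.

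The cost is a change in the scale of the odds ratio and an amendment of the protocol wording. Because the primary test changes, this plausibly counts as a substantial amendment under {25} and would then need a new ethics opinion.

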### Interim analyses {21b}

Not applicable. No interim analysis is planned.

### Methods for additional analyses (e.g. subgroup analyses) {20b}

Not applicable. No additional analyses are planned.

### Methods in analysis to handle protocol non-adherence and any statistical methods to handle missing data {20c}

In case of missing values, multiple imputation methods will be applied for the mRS score and the imputed values will be used to determine the dichotomized outcome. In addition, a sensitivity analysis will be performed treating the patients with missing score values as having an “unfavourable” outcome and also treating only the complete cases.

For analysis of the overall effect of therapy, the outcome of all patients with missing data for the primary outcome at 12 months will be counted as unfavorable.

### Plans to give access to the full protocol, participant-level data, and statistical code {31c}

Individual participant data will be available on reasonable request. Individual participant data (including data dictionaries) that underlie results concerning primary or secondary endpoints reported in a published scientific article will be shared on demand after deidentification. The data will be shared beginning 6 months and ending 3 years following article publication. Data are made available to researchers after a methodologically sound scientific proposal has been submitted to the coordinating investigator and a steering committee, consisting of the coordinating investigator, the representative of the coordinating investigator, and a SZB member, has approved the proposal, and a data access agreement has been signed. The study protocol and the informed consent forms will be made available on demand.

## Oversight and monitoring

### Composition of the coordinating center and trial steering committee {5d}

To ensure accurate, complete, consistent, and reliable data, the investigator’s site(s) and trial procedures will be monitored by a representative of the project leader. The project leader’s representative will visit the site:To evaluate the progress and recruitment of the trialTo review the source documents and CRFs for protocol compliance, accuracy, and validationTo assess facilities and equipmentTo check for protocol complianceTo assure the AE documentation

Source data verification will be performed in order to verify the accuracy and completeness of the entries on the case report form (CRF) by comparing them with the source data and to ensure and increase the quality of the data. All data which are subject to SDV must have been entered in the medical record or, in the case of source documents, enclosed with the medical record. The investigators will afford the CRA access to the medical records for the performance of SDV.

The frequency and scope of the monitoring visits will be defined in the Monitoring Plan for this trial which also includes the extent of source data verification that is required.

### Composition of the data monitoring committee, its role, and reporting structure {21a}

The Data Safety Monitoring Board (DSMB) is an independent committee monitoring the study progress of the safety of trial participants and the quality of the collected data (by monitoring reports) and should make recommendations on the discontinuation, modification, or continuation of the trial. The tasks of the DSMB in the trial are the following:

The DMSB will review all SAEs of all patients so far recruited to the trial regularly.

The coordinating investigator can ask the DSMB at any time to review any data from the trial and to decide whether to proceed with the trial without changes, to modify the trial, or to stop the trial entirely. The data provided to the DSMB for review may also include so far unmonitored data.

The DMSB is free to suggest any modifications regarding the trial (e.g., stopping of the trial, modifications of the protocol).

The DSMB will include at least 3 members with experience in the conduct of the study and individual expertise in the field of neurology and biometrics. Further details concerning members, function, reports, and modalities of meetings are provided by the DSMB Charter of this trial.

The Data Safety Monitoring Board (DSMB) has been appointed to review the conduct and results of this trial at 2 enrolment landmarks (after 50 and 100 of the patients have been enrolled). The DSMB is charged with reviewing safety data in both arms of the trial. The DSMB will be empowered to stop the study for evidence of harm but not for evidence of lack of efficacy. The DSMB is also asked to offer perspective on any therapeutic or diagnostic testing advances that may occur during the course of the trial that may influence the outcome. If protocol modifications are warranted, close consultation among the DSMB, the SZB staff, and the study leadership will be required. Further details are provided in a separate DSMB charter.

### Adverse event reporting and harms {22}

Any AE defined in the trial protocol as relevant for the evaluation and analysis of the clinical trial has to be documented in the CRF on the respective adverse event report form. The following criteria will be assessed: type, beginning, end, and outcome of the event (recovered, improved, unchanged, recovered with sequelae, worsened death, unknown). Pregnancy is not an exclusion criterion in this lifesaving treatment study.

All safety evaluations will be performed on the ITT population, which consists of all patients who were randomized. Frequency tables and/or summary statistics will be provided as described below for the observed adverse events (AEs) and for patients having a respective AE:Per system organ classesPer preferred termsTherapy-related AEsSerious AEs related to therapy

### Frequency and plans for auditing trial conduct {23}

In accordance with ICH GCP, this trial may be selected for audit by representatives of the project leader.

The investigator agrees to give the auditor access to all relevant documents for review and to support the project leader to solve possible audit findings concerning the trial conduct at the respective site.

After every audit, the auditee(s) will receive an audit confirmation by the auditor. This document has to be filed together with the trial documentation.

At the end of the trial, a copy of the audit certificate(s) will be included in the final report.

